### Interventions

The SET intervention consists of four elements:House modification. Any open eaves or gaps in the walls will be sealed with concrete. Windows will be screened and damaged doors will be repaired with wood.Eaves tube installation. A 20 cm long piece of PVC pipe with a diameter of 15 cm (the eave tube) will be installed at 1.5 - 2 m intervals into the outer walls of occupied rooms (e.g. bedrooms and living rooms but not storage rooms). The target location will be approximately 20 cm below the roof, but this may need to be adapted depending on different house designs.Maintenance. The condition of the SET intervention will be monitored through village ‘walk-throughs’ every two months, when any damage to window screening, eave tubes, doors, or walls will be recorded and repaired.Insecticide treatment and retreatment. The eave tube inserts will be treated using a commercially available, 10% wettable powder formulation of the pyrethroid insecticide beta-cyfluthrin (Tempo Ultra WP, Bayer). Inserts in the study will be replaced with freshly treated inserts if bioassay mortality falls below 70%.

Persistence of the insecticide will be monitored by monthly bioassays with local, field-collected mosquitoes. These bioassays will consist of an eave tube with the insert placed at the end of the tube. A bottle filled with hot water and covered with a worn sock will be placed behind the insert to act as a host cue. Local, field-collected 2–5 day old female *An. gambiae s.l.* mosquitoes will be allowed to recruit freely to the insert for one hour and knock down and mortality will be assessed 24 h post exposure.

LLINs (Permanet 2.0; Vestergaard Frandsen, Switzerland) will be distributed at universal coverage to each household in all of the study villages. Côte d’Ivoire’s national malaria control program (NMCP) guidelines will be followed to encourage consistent and correct use of the LLINs. During the routine visits to villages for epidemiological and entomological monitoring, trial staff will administer standardized questionnaires, including questions on the presence of LLINs in the sleeping areas and their use by the household.

### Epidemiological evaluations

Children enrolled in the ACD cohort will receive routine visits from the study team (a trained nurse and the CHW) every two weeks (rainy season) or every month (dry season).

At the first visit, additional data will be collected on household level socioeconomic indicators, methods of vector control used in the household, and sleeping habits. Children five years of age or younger will have a blood sample taken for immediate measurement of hemoglobin levels using a spectrophotometer (HemoCue Hb 201+, Radiometer Medical Aps, Ängelholm, Sweden). All children will receive a three-day course of a first-line antimalarial recommended by the NMCP in Côte d’Ivoire (artesunate-amodiaquine or artemether-lumefantrine), to clear any existing malaria parasite infection. The study team will observe adherence for the first dose and parents or guardians will be instructed to complete the treatment at home. The CHW will be instructed to check compliance and the parents or guardians will be asked to bring the empty drug packet to the following visit. A thick blood smear will be taken on the next visit (two weeks later) to confirm parasite clearance.

At all visits, the child’s axillary temperature will be recorded. If the child is febrile (axillary temperature ≥ 37.5 °C), or has a history of fever in the past 48 h, or if the parents report that the child is sick, a health exam will be carried out and a record will be made of the child’s symptoms, pulse, and respiratory rate. A blood sample will be taken from febrile children by finger prick for a malaria rapid diagnostic test (mRDT; SD Bioline Malaria Ag P.f./Pan, Standard Diagnostics, Inc., Gyeonggi, Republic of Korea). A thick blood smear and a blood spot on filter paper will also be taken for subsequent confirmation of the infection. If the mRDT is positive and the study nurse diagnoses uncomplicated malaria, the child will be treated with a first-line antimalarial (artesunate-amodiaquine) for three days, according to the guidelines of the NMCP. Treatment for malaria will be provided free of charge through this system. If the child exhibits any symptoms of severe illness, he or she will be sent immediately to the closest health clinic for treatment. Once a month, a thick blood smear and blood spot will be taken from all children in the cohort to monitor for asymptomatic parasite infections. During these visits, a record will be made of recent travel, and whether the child slept under an LLIN the preceding night.

Four times during the course of the monitoring period, at the start and end of the rainy season, all children in the cohort will be checked for respiratory symptoms (cough, nasal discharge, rales, elevated age specific respiratory rate, and chest indrawing) and children five years of age or younger will have a blood sample taken for immediate measurement of hemoglobin levels using a spectrophotometer. One year after the initial parasite clearance, at the start of the next rainy season, all of the cohort children will again be cleared of malaria parasites with a three-day course of front-line antimalarials (artesunate-amodiaquine), confirmed by thick blood smear on the following visit.

To capture any malaria cases that occur between cohort visits, the parents or guardians will be given a card at the initial visit, identifying the child as a participant in the study, with instructions to present this card whenever the child receives medical treatment between visits. The back of the trial card will provide space to record the date of visit and the diagnosis.

### Entomological evaluations

Each month, mosquitoes will be sampled using human landing catches (HLC) both indoors and outdoors for one night at four randomly selected houses in each of the 40 study villages. Starting at 18:00, one capturer will sit inside of the house in the living room area and one will sit outside of the house. These capturers will collect mosquitoes on their bare feet and legs using small glass tubes, which will then be plugged with cotton and brought back to the laboratory. A supervisor will pass by every hour to ensure that the capturer is awake and following the correct capture protocol. At 01:00, a second team will take over and continue the captures until 08:00. When the HLC samples are brought back to the lab, the mosquitoes will be identified using a species key based on morphological traits [28]. A subset of the captured *An. gambiae s.l.* and all *An. funestus* and *An. nili* females will be dissected to determine parity. Both species are known to be vectors of malaria in Côte d’Ivoire [29–31], however *An. gambiae s.l.* is the numerically dominant vector in the trial area [32]. After dissection, mosquitoes will be preserved for later PCR analysis to determine sporozoite prevalence. PCR will also be used to type *An. gambiae s.l.* females to species, and to measure the prevalence of *kdr* and *ace-1* resistance mutations.

In addition to the HLC sampling, CDC light traps will be placed every other month in 12 randomly selected houses for one night in each village. These traps will be set in the sleeping area at 18:00 and removed the following morning at 08:00. The study team members will record the number of people who slept in the room during the trap night, the number of LLINs installed in the sleeping area, and whether the people reported sleeping under the available LLINs during the trap night. The mosquitoes captured in the traps will be brought back to the laboratory for morphological species identification.

To monitor resistance in the study area throughout the course of the trial, larval dips will be used to collect *An. gambiae* larvae from eight study villages (four per arm). These field-collected larvae will be reared to adulthood in the insectary at IPR, and bioassays will be conducted with 2–5 day old females. WHO insecticide susceptibility bioassays will be conducted using diagnostic concentrations of the active ingredient in the LLINs (deltamethrin) and the eave tubes (beta-cyflutherin). CDC bottle bioassays will also be done with both actives, to measure resistance intensity. A susceptible *An. gambiae* lab strain (Kisumu) will be tested as a control in these bioassays. After the bioassays, surviving mosquitoes will be put in RNAlater and stored at -80 °C for subsequent microarray analysis to monitor expression of genes potentially involved in metabolic resistance.

### Social science

During the trial, data will be collected on perceptions of and willingness to adopt the SET intervention, knowledge relating to the SET intervention, and attitudes and emotions relating to malaria and new malaria prevention interventions. These data will be collected using three complimentary methodologies: (1) questionnaires administered to homeowners and heads of household, (2) ethnographic studies (observation and informal discussion), and (3) focus groups.

The questionnaires will be administered before the installation of the intervention and at the end of the monitoring period in the six villages designated for social science activities (see [33] for more details on the methodology for these activities). Questionnaires will also be administered in two of the villages midway through the monitoring period. The ethnographic studies will be conducted during and directly after the SET installation process, and during the installation of insecticide treated inserts in three villages in the SET arm. Focus group discussions will be held midway through the monitoring period with people drawn from diverse demographic groups (mothers, village leaders, young adults) in two SET + LLIN villages and one LLIN village.

### Economics

Data on the incremental financial and economic costs of SET will be collected alongside the intervention and attributed to either housing modification (screening, closing eaves), eaves tube installation, SET maintenance, or treatment and retreatment of inserts with insecticide. Where resources (e.g. staff) are shared between more than one element, costs will be allocated using a suitable proxy. Costs for research activities will be excluded. Financial costs will be obtained from project expenditure records. Economic costs (including financial expenditure and donated resources) will be identified from project records and via social science activities, with a value for donated resources being imputed from market rates. Capital costs will be annualized over their useful life (financial costing) and annualized at a discount rate of 3% in the economic costing.

The numbers of malaria cases averted in the SET + LLIN arm compared to the LLIN only arm will be used to calculate disability adjusted life years (DALYs) averted using standard methods [34]. If the epidemiological data suggest an effect on anemia and/or respiratory infections, this will also be included in the DALY calculations.

### Trial oversight

A Trial Steering Committee (TSC) will be established to provide oversight of the study. TSC members will be independent of the trial and its institutions, and have the necessary expertise to monitor study progress and participant safety. The TSC will be responsible for monitoring the progress of the trial, adherence to protocol, patient safety, and for consideration of new information. The TSC will also have access to the study data at regular intervals to determine if additional interim analyses of trial data should be undertaken, and assess any safety issues that may arise during the study. The TSC can make the decision to stop the study at any point.

Day-to-day management of the trial is the responsibility of the chief investigator and co-investigators. They will maintain appropriate medical and research records, in compliance with Good Clinical Practice (GCP), and all regulatory and institutional requirements. Standard Operating Procedures (SOPs) will be developed in accordance with Good Clinical Practice (GCP) and Good Field Entomology Practice (GFEP). An independent consultant will review study protocols, SOPs, and QA reports. A study monitor will conduct audits at key phases of the study.

### Safety considerations

The LLINs distributed as part of this trial (Permanet 2.0) have been fully evaluated by the WHO Pesticide Evaluation Scheme (WHOPES) and are routinely distributed by the NMCP in Côte d’Ivoire.

The beta-cyfluthrin used on the eave tube inserts is a pyrethroid insecticide, which typically have low mammalian toxicity and good safety profiles. The trial will use a commercially available formulation of the insecticide. The inserts will be machine treated to minimize contact with the insecticide dust. All personnel responsible for treating and installing treated inserts will be provided with the appropriate personal protective equipment (PPE).

In addition to safety considerations relating to the use of insecticides, concerns have previously been raised with regards to house modifications and the possibility that they might increase risk of acute respiratory infections due to changes in the indoor environment [12]. To monitor for adverse events (AEs), regardless of whether they are due to insecticide use or house modifications, children enrolled in the ACD cohort will be monitored at each visit for symptoms including skin irritation, respiratory problems, headaches, fatigue, and nausea. The nurses responsible for the ACD visits will record these or any other adverse events, and report them to their supervisor. AEs occurring in non-cohort children living in the study villages will be recorded through passive monitoring of visits to the local health facilities and the CHWs. If a parent or guardian agrees to participate, a verbal autopsy using an established questionnaire will be conducted after any deaths in the cohort. The host institution (IPR) medical expert and his clinical team will be responsible for recording, reporting, and managing AEs and SAEs, including follow-up, in accordance with national guidelines. A report on AEs and SAEs, including deaths in the cohort, will be provided regularly to the TSC.

HLC capturers will be vaccinated against yellow fever free of charge if they do not already have proof of yellow fever vaccination. If they become sick with malaria at any point during the trial, they will be provided treatment free of charge at the nearest health facility.

### Handling of drop-outs / withdrawals

Participants are free to withdraw from the study at any point for any reason. Participants include children in the ACD cohort, households where entomological monitoring is conducted, and capturers conducting HLCs. For children in the ACD cohort, the reason for premature termination or withdrawal will be documented – e.g., SAE, withdrawal of consent, loss to follow up. If the child withdraws from the cohort for any of these reasons, another child will be selected to replace them, preferably in the same age group and from the same household but if that is not possible, then from another randomly selected household.

## Study endpoints

### Epidemiological

The primary endpoint of the trial will be the incidence of clinical malaria determined by active case detection in children six months to ten years of age. Clinical malaria will be defined as an axillary temperature of ≥37.5 °C combined with a positive mRDT. The secondary clinical endpoints will be: (1) incidence of asymptomatic malaria infection detected by microscopy and/or PCR, (2) prevalence of anemia in children five years of age or younger (measured four times during the study), and (3) incidence of the following symptoms of respiratory infection: cough, nasal discharge, rales, elevated age specific respiratory rate, and chest indrawing.

### Entomological

The primary entomological endpoints will be the mean number of malaria vectors (*An. gambiae s.l.*, *An. funestus*, and *An. nili*) captured per person per night both indoors and outdoors by HLC, and the mean number of malaria vectors captured indoors per trap per night by CDC light trap. The secondary endpoints will be: (a) the entomological inoculation rate (EIR) for *An. gambiae s.l.*, *An. funestus*, and *An. nili* calculated as the mean number of sporozoite infective bites/person/year, (b) parity of *An. gambiae s.l.*, *An. funestus*, and *An. nili*, (c) the prevalence (% mortality using a diagnostic dose) and strength (LD50 and resistance ratios) of insecticide resistance to deltamethrin and beta-cyfluthrin measured before, during, and after the trial period in *An. gambiae s.l*.

### Social science

The social science endpoints will be the percentage of homeowners who consent to the SET intervention when offered, and the degree to which consent can be predicted based on psychosocial predictors. In addition, observations and discussions on attitudes towards the technology will be considered in anticipation of diffusion and scale up of the technology to other communities.

### Economics

The economic endpoints will be marginal economic and financial cost per malaria case averted and the cost per DALY averted of the SET intervention compared to LLINs alone.

## Sample size rationale

### Epidemiological

The epidemiological impact of SET alone or in combination with LLINs is currently unknown. A minimum effect size of 40% was used in the sample size calculations, which is similar to the effect size used in other sample size calculations for house-based malaria interventions [12, 35]. The mean incidence of clinical malaria in the reference arm was assumed to be 0.5 malaria cases per child per year, based on existing data from the study area. Further assuming a coefficient of variation (k) of 0.5, (a conservative estimate for a high transmission setting), 80% power and significance level of 5%, requires 20 clusters per arm and 50 children per cluster to be followed for two years (encompassing 2 peak transmission seasons).

### Entomological

Pilot studies in semi-field systems in Tanzania and Kenya suggest an up to 80% reduction in mosquito entry into houses with eave tubes and screening [20, 21]; a more conservative 50% reduction was used for these sample size calculations. Again, this is consistent with other RCTs testing the effect of house modifications on entomological endpoints [12, 13]. A baseline survey conducted during the dry season in the study area had mean HLC catches of 23.5 *An. gambiae*/trap/night, with SD = 17 and intraclass correlation (ICC) = 0.84. For 80% power to detect a 50% drop in mean mosquito densities of 23 mosquitoes at the 5% significant level, 7 households need to be sampled in each of the 40 villages. To capture the substantial seasonal changes and to accommodate available resources, 4 randomly selected households will be sampled over one night in each village every month, powered to detect a difference for every two months of pooled data.

CDC light traps consistently caught fewer mosquitoes than the HLC during the baseline survey, with a mean nightly catch of 2.5 *An. gambiae*, a log SD of 1.7 and ICC = 0.229. To detect a 50% reduction mosquito density with 80% power at the 5% significance level requires 12 households per cluster. In order to capture seasonal variation in mosquito density, collections will be performed every two months.

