### Study design

The study design is summarized in Fig. 2 and a schedule of trial activities is presented in Table 1. The design is a two-armed CRT with 20 villages (clusters) per arm. Villages will be allocated to an arm through restricted randomization. Villages in the control arm will receive universal coverage of LLINs, while the villages in the treatment arm will receive universal coverage of LLINs and heads of household living in suitable houses will also be offered the SET intervention free of charge. The target coverage for SET in the treatment arm is ≥65% of all houses in the village. After the installation of SET (in the treatment arm) and the distribution of LLINs (in both arms), the epidemiological and entomological monitoring will begin.

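### The CDC light-trap sample size does not give its stated 80% power: 12 houses in 20 villages per arm give about 66% per collection round, and no number of houses reaches 80%

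*Protocol article*

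**What the plan says.** Under Sample size rationale, Entomological, the target for both trapping methods is a halving of mosquito density: "a more conservative 50% reduction was used for these sample size calculations".

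For CDC light traps the baseline survey is reported as a mean nightly catch of 2.5, a log SD of 1.7 and an ICC of 0.229. From this the protocol concludes: "To detect a 50% reduction mosquito density with 80% power at the 5% significance level requires 12 households per cluster". Collections are repeated every two months, and the reason given is seasonal variation, not power.

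For HLC the inputs are "mean HLC catches of 23.5" per night, "with SD = 17 and intraclass correlation (ICC) = 0.84", and the conclusion is "7 households need to be sampled in each of the 40 villages". This is carried out as four houses a month, described as "powered to detect a difference for every two months of pooled data".

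The number of clusters is fixed under Study design: "The design is a two-armed CRT with 20 villages (clusters) per arm". Study endpoints, Entomological, lists the light-trap density and the HLC densities together as primary entomological endpoints.

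**The concern.** The household counts are offered as what 80% power requires, while the number of villages is already fixed at 20 per arm. In a cluster trial, extra houses in the same villages run into a ceiling set by the ICC. If that ceiling lies below what is needed, no household count is correct.

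Light traps matter here because, under Randomization and blinding, they are the density measure chosen to depend less on the collector in a trial that cannot be fully blinded. A reader who trusts the stated 80% would take the chance of missing a true halving in one round to be 20%. On the protocol's inputs it is about 34%.

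**Working it through.** **Inputs** (Sample size rationale, Entomological, and Study design): c = 20 villages per arm; m = 12 houses per village; SD = 1.7 on the log scale; ICC = 0.229; 50% reduction, so d = ln 2 = 0.693; 5% level; 80% power. Sidedness is not stated, so two-sided is assumed and one-sided is also tried. (z₀.₉₇₅ + z₀.₈₀)² = 7.849.

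**Light traps: trying to reproduce 12 houses**

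1. Independent observations needed per arm: 7.849 × 2 × 1.7² / 0.693² = 94.4.
2. Design effect: 1 + (12 − 1) × 0.229 = 3.519.
3. Effective observations per arm: 20 × 12 / 3.519 = 68.2, short of 94.4.
4. Standard error of the log ratio: 1.7 × √(2/68.2) = 0.291.
5. Power: Φ(0.693/0.291 − 1.96) = Φ(0.42) = 66.3% (64.1% with a t distribution on 38 df).
6. Ceiling as m grows without limit: 20/0.229 = 87.3 effective observations, still below 94.4; power 76.9%.
7. Detectable reduction at 12 houses: 1 − exp(−2.80 × 0.291) = 1 − exp(−0.82), about 56%.
8. Villages per arm needed at 12 houses: 94.4 × 3.519 / 12 = 27.7, so about 28 (29 if one cluster is added as a small-sample correction).

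**Other readings of the same inputs**

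| Reading | Power at 12 houses | Houses for 80% |
|---|---|---|
| Two-sided, ln scale | 66.3% | none |
| One-sided | 76.9% | about 20 |
| ln(x + 1) | 32.9% | none |
| log10 | 17.7% | none |
| 1.7 as a variance | 87.4% | 6 |
| 1.7 as a raw SD, d = 1.25 | 99.0% | 2 |
| 40 villages per arm | 92.0% | 4 |

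None returns 12. For 12 houses to give 80%, the log SD would have to be about 1.44, or the ICC about 0.14.

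**HLC: does 7 houses reproduce?** Use the standard cluster formula for means with a constant between-village coefficient of variation k.

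- Between-village SD: 17 × √0.84 = 15.58, so k = 15.58/23 = 0.68.
- Within-village variance: 0.16 × 17² = 46.2 in each arm.
- Villages per arm at m = 7: 1 + 7.849 × [2 × 46.2/7 + 0.68² × (23² + 11.5²)] / 11.5² = 19.8 (unrounded k).
- With 20 villages per arm, power is 79.2% at 4 houses, 80.2% at 6, 80.4% at 7 and 80.6% at 8.

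The HLC figure therefore stands on this reading, although 6 houses would already suffice.

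**The case against.** **The HLC figure looks wrong in the same way.** A reader might infer that both counts fail. If the SD stays at 17 in the SET arm while the mean falls from 23 to 11.5, 7 houses give 63.4% and the ceiling is 64.6%. But the protocol does not state that assumption. Its own clinical sample size uses a coefficient of variation, and its entomological analysis uses Poisson or negative binomial models, in which variance falls with the mean. On the constant-k reading, both the 7 houses and the two-month pool of 8 reach 80%. The documents therefore do not support replacing the HLC figure with 63%, or deleting the two-month statement. What remains is small: at an ICC of 0.84, HLC power depends on the variance assumption far more than on the number of houses.

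**The same rescue for light traps.** It is not available. Their SD is already on the log scale, where a proportional reduction leaves it unchanged.

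**The analysis may pool rounds.** This is the strongest reply. The analysis section names no per-round test, and collections recur every two months for two years, about 12 rounds. The documents give no between-round correlation, so pooled power can only be shown over an assumed range. Let ρ be the correlation of a village's effect between rounds, with new houses each round and a constant treatment effect. The variance of a village mean is then 1.7² × [0.229 × (ρ + (1 − ρ)/12) + 0.771/144]. Power is about 76% at ρ = 1, 84% at ρ = 0.8 and 95% at ρ = 0.5. The pooled comparison may well be adequate. That limits the consequence but does not make the printed sentence right, because it ties 80% to 12 households with no mention of rounds.

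**The 50% effect might be called optimistic.** The best pilot figure diluted by coverage is 0.65 × 80% = 52%. But 65% is a minimum target, and 52% still exceeds 50%, so this does not show an error.

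**Conclusion.** The light-trap statement is wrong as written. On the protocol's own inputs, two-sided power per round is about 66%, not 80%. The ceiling is about 77%, and the reduction detectable with 80% power is about 56%. The result assumes a two-sided 5% test, equal log SD in both arms, 20 villages per arm and the usual design effect. A one-sided test raises power at 12 houses to about 77%, still short.

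The conclusion covers one collection round only. It does not show that the comparison over two years is underpowered, and it does not extend to HLC. Its weight is moderate: a primary entomological endpoint is affected, but the clinical primary endpoint and its sample size are not.

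**What to change.** Keep the sampling and replace the light-trap sentence with one to this effect: with 20 villages per arm, 12 houses per village, a log SD of 1.7 and an ICC of 0.229, one collection round has about 66% power (two-sided 5%) to detect a 50% reduction, or 80% power to detect about 56%.

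If the count of 12 came from a different SD, ICC or formula, print those inputs instead so that it can be reproduced. If 80% power is meant for the comparison over all rounds, say so and state the between-round correlation assumed.

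Leave the HLC figure as it is. A clause saying that it assumes a constant between-village coefficient of variation would be a useful addition.

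The cost is a few lines of text and a less favourable stated power. No extra villages, houses or collections are needed.
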